## Abstract

**Background:**

Visual loss following stroke impacts significantly on activities of daily living and is an independent risk factor for becoming dependent. Routinely, allied health clinicians provide training for visual field loss, mainly with eye movement based therapy. The effectiveness of the compensatory approach to rehabilitation remains inconclusive largely due to difficulty in validating functional outcome with the varied type and dosage of therapy received by an individual patient. This study aims to determine which treatment is more effective, a standardized approach or individualized therapy in patients with homonymous hemianopia post stroke.

**Methods/Design:**

This study is a double-blind randomized controlled, multicenter trial. A standardised scanning rehabilitation program (Neuro Vision Technology (NVT) program) of 7 weeks at 3 times per week, is compared to individualized therapy recommended by clinicians.

**Discussion:**

The results of the trial will provide information that could potentially inform the allocation of resources in visual rehabilitation post stroke.

**Trial Registration:**

Australia and New Zealand Clinical Trials Register (ANZCTR): ACTRN12610000494033

## Background

Stroke is a leading cause of disability [1], and approximately 30-35% of people with stroke have a homonymous hemianopia [2]. Hemianopia is described as "blindness in one half the field of vision in one or both eyes" [3]. Literature suggests that natural recovery occurs in 50% of people, mostly in the first month with minimal recovery taking place after 6 months [2]. Visual loss, following a stroke can be temporary or permanent, and interfere with an individual's ability to perform daily living activities and live independently [4].

Visual training in homonymous hemianopia post stroke is recognized as an important part of rehabilitation [5]. The project described in this manuscript is comparing the effects of two approaches to treating visual field loss in the subacute rehabilitation phase (week two - six months) following a stroke. Currently rehabilitation employs three key strategies including optical devices, compensatory training and visual restitution therapy [6]. The first strategy is to use optical devices, such as prism glasses, to displace the visual image. The efficacy of prisms has not been demonstrated due to the lacking of a standardized methodology and few controlled studies [7].

The second strategy is compensatory and aimed at enhancing eye movements and/or head movements. This takes a number of different forms including the training of oculomotor or saccadic movements, on a standardised computer screen, or devices such as the Dynavision [8], which incorporates a larger visual area, where head movements are required. Oculomotor scanning performance, thus only requiring eye movement, has been linked to subjects reported visual difficulties in everyday life [9]. Training of oculomotor or saccadic movements has been demonstrated to lead to an improved visual search field and reading ability [10-12]. No large scale randomized controlled trials have been performed to date to validate this intervention [13]. Dynavision training has been demonstrated to lead to improvement in visual scanning in a single case study [14], and in a descriptive study of driving [15], but not in a small controlled study of driving in stroke [16].

The third strategy uses visual restitution therapy and aims to enhance neuroplasticity [17]. This method involves the stimulation of the 'borderzone' or 'transition zone' between the area of visual loss and the intact area of vision [18]. A systematic review found [13] inconclusive evidence to support visual restitution based therapy as a means of restoring visual fields following brain damage.

In Australia, most visual training employs compensatory eye and head movement based therapy but current delivery of vision rehabilitation is recommended by treating therapists and is thus subjective [19]. Therapies can vary from a comprehensive combined static and mobility training to the prescription of magnifiers to help with reading with minimal instruction of their use. Due to the wide variability in type and dosage of therapy received by an individual patient, the benefits of visual training in terms of compensation and improved performance in functional tasks are uncertain [20].

In response to the need for a structured therapy program of visual training in homonymous hemianopia post stroke, the Neuro Vision Technology (NVT) program has been developed which is a standardized therapy and involves both a static scanning training and a dynamic mobility component. The static scanning component uses the NVT device, (see figure 1) to assess for the presence of neurological vision impairment, such as a homonymous hemianopia and/or visual spatial neglect. A standardized presentation of colored lights (LEDs) is displayed on a horizontal panel, placed at eye level approximately 30 cms from the patient. The panel of lights extends approximately 80 cms either side of central fixation, with the lights at the ends of the panel subtending an angle of approximately 70 degrees from midline. In the presence of a homonymous hemianopia the patient is required to use both head movement and eye movement towards the affected visual field to detect the light stimulus.

**Figure 1 F1:**
[figure not shown]
**NVT Scanning Device**.

The NVT scanning device is used in rehabilitation to teach a pattern of systematic visual search strategies from the perimeter of the affected visual field towards the intact visual field. It aims to improve the patient's awareness and understanding of the nature of their vision impairment. The NVT training program then transfers visual scanning strategies, established using the NVT scanning device, into tasks that are mobility based. This developed NVT training differs from the other compensatory techniques as it involves a larger real visual world, whereas other compensatory training is aimed at rehabilitating reading abilities using a computer screen. NVT training has not been evaluated in terms of its effectiveness in rehabilitation for people with hemianopia.

To determine the most effective rehabilitation for people who have a hemianopia after stroke, it is necessary to examine the effects of the standardized and non-standardized rehabilitation strategies on performance in daily activities. We aim to compare the effectiveness of the standardized NVT program versus current individualized therapy as recommended by treating clinicians in patients with homonymous hemianopia post stroke.

## Methods and design

The study design is a single-blind randomized, controlled trial in Adelaide, Australia, which will be conducted over 12 months. The intervention design is summarised in Figure 2.

**Figure 2 F2:**
[figure not shown]
**Study Design**.

### Randomized controlled trial

#### Participants

Patients will be included if they have had a stroke occurring a minimum of two weeks and a maximum of six months prior to the commencement of assessment; homonymous hemianopia (any field loss reached above and below the horizontal axis, as measured by Medmont C-100 perimetry [21] performed by a neurophthalmologist); score of 25 or more on the Mini Mental State Examination (MMSE) [22]; have corrected vision of at least 6/18; be able to mobilise a distance of 35 metres independently or with supervision or standby assistance; and be over 18 years of age. Formal assessment related to the inclusion criteria is detailed in Figure 2.

Patients will be excluded based on evidence of aphasia or poor English language skills that significantly impact on understanding instructions.

#### Setting/Locations

Participants will be recruited from acute hospitals, rehabilitation hospitals and outpatient settings in Adelaide, Australia.

#### Procedures/Measurements

All outcome assessments will take place face to face with participants by assessors who are blind to the allocation group. All outcome assessments (listed in Figure 2) will be performed by mobility instructors in vision rehabilitation who have received training in the standardized use of the tools.

#### Recruitment

Participants will be recruited from all three publicly funded rehabilitation facilities in Adelaide. In addition we will recruit from private rehabilitation facilities, neurophthalmologists and the two non government organisations who provide training for visual impairment in South Australia, Australia.

#### Randomization

Randomization is managed by the pharmacy department at the Repatriation General Hospital. A statistician external to the study will generate the random sequence using the random number generator in Microsoft Excel and created sequentially numbered, sealed envelopes containing group allocation for participants.

#### Intervention 1

Those participants who are randomized to the intervention group 1 will receive the standardized NVT program that consist of: three weeks static scanning training using the NVT scanning device and four weeks of mobility training using NVT scanning techniques.

All assessment and training tasks using the NVT scanning device are standardized using the Vision 2000 software program. Patient responses to the light stimulus are also recorded in a manner that allows for uniformity of performance measurement. The assessment process initially uses single light presentations to determine the patient's degree of spontaneous scanning into the affected field, and the degree of visual field loss. Subsequent light sequences utilize multiple lights in exercises, which are graded in complexity. Patient responses to these exercises are indicative of their ability to attend to multiple stimuli, their ability to adopt a systematic search pattern, the speed at which visual stimuli can be detected and the ability of the patient to utilize spatial reasoning to compare light patterns. The NVT assessment on the scanning device informs the NVT training process.

The NVT scanning device is used to teach a pattern of systematic visual search strategies from the perimeter of the affected visual field towards the intact visual field. These training exercises utilize patterns of lights that reinforce an efficient and functional speed of scanning to allow for accurate detection of all stimuli. Refer to Figure 1.

The NVT training program then transfers visual scanning strategies, established using the NVT scanning device, for example the amount of head turning and frequency, into the real world while walking, with the aim being for these strategies to become automatic. Scanning skills are graded from an environment that is structured and familiar to the patient, into more dynamic busy environments including shopping centres, where high level scanning skills and complex visual processing is required. Training will occur three times per week for 7 weeks. Audiovisual information of the intervention and NVT device is accessible through the following link: http://www.scivee.tv/node/16116.

#### Intervention group 2

Participants in intervention group 2 will receive individualized, or non-standardized therapy recommended by clinicians or usual care. "Usual care" for people receiving rehabilitation after stroke varies across inpatient and ambulatory rehabilitation units. However, intervention currently available includes one to one occupational therapy and mobility instruction that promotes visual scanning, activity of daily living skills, and mobility training from a non government organization, separate from health services, the Guide Dogs Association SA.NT. Techniques for intervention include pen and paper tasks, scanning training on light boards, compensatory training in activities of daily living and mobility. Dosage and type of therapy will be determined by the treating clinician and recorded. This group will be wait-listed for the NVT training which will be offered at the completion of the three month follow up.

#### Outcomes

As walking ability is a skill which is valued by those who have suffered a stroke and is required for safe discharge from hospital our primary outcome will be performance on the Mobility Assessment Course (MAC) [23] after three months. The MAC assesses performance on a mobility course with targets positioned on the walls along the course. Participants are scored on the number of targets they identify and the time taken to complete the course. The MAC, along with the Visual scanning analyzer (VSA) [23], were designed to test visual scanning. The MAC measures the extent to which a person visually scans and identifies hazards when walking, and has been validated with stroke patients [23]. In this validation study [23] the MAC included a measure of obstacle avoidance, which mobility evaluations generally include, however the results concluded that this was a poor measure of visual neglect in this population and thus was not used in MAC data collection in this study protocol.

The secondary outcome assessments will provide a broader picture of function and quality of life following a stroke and include Visual scanning analyzer (VSA) [23], Pepper Visual Skills for Reading test [24], National Eye Institute Visual functioning Questionnaire (NE1 VFQ-25) [25], Veteran Low Vision Visual Functional Questionnaire 20 (VA LV VFQ 48) [26], Mayo-Portland Adaptability Inventory (MPAI) [27] and the Rivermead Behavioural Inattention test (BIT) [28] as listed in Figure 2.

#### Sample size

Sample size has been calculated based on data reported in a pilot study validating the primary outcome measurement tool, the Mobility Assessment Course [23]. The minimum number of participants required is 20, with 10 in each of the two groups providing 80% power (alpha level 0.05) to detect a mean difference 0.63 on scores, assuming the standard deviation is 0.74. Analysis of the results is planned in 2010 and will be undertaken by statisticians blind to the group allocation.

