#### Statistical analysis

Data will be entered into an SPSS database with all identifying details removed. An ANCOVA will be performed to compare outcomes between the intervention groups, controlling for initial scores as covariates in the analyses.

Statistical analyses will be undertaken using SPSS version 17.0 Statistical software. All analyses will on an intention to treat basis and will be blinded (i.e. groups identified by number only) and results published according to the Consort Statement formal.

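### The stated 80% power does not follow from the plan's own inputs: 10 per group gives about 44% in an unadjusted two-sided comparison, and 80% needs 23 per group

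*Protocol article*

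**What the plan says.** The protocol article's Sample size section bases the calculation on an earlier study of the outcome tool: "Sample size has been calculated based on data reported in a pilot study validating the primary outcome measurement tool, the Mobility Assessment Course". It then states "The minimum number of participants required is 20, with 10 in each of the two groups providing 80% power (alpha level 0.05", and names the target: "to detect a mean difference 0.63 on scores, assuming the standard deviation is 0.74". It does not say whether the test is one-sided or two-sided, and it mentions no baseline correlation, variance reduction or dropout allowance.

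The Outcomes section fixes the endpoint to which this applies: "our primary outcome will be performance on the Mobility Assessment Course (MAC) [23] after three months". The Statistical analysis section gives the method: "An ANCOVA will be performed to compare outcomes between the intervention groups, controlling for initial scores as covariates in the analyses". Neither section links the ANCOVA to the sample size.

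**The concern.** A standardized difference of 0.85 is large, but 10 per group is too few to detect it with 80% power when two independent groups are compared. The sentence gives every input needed for the check, so the power can be recomputed without any outside source.

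This sentence is the only justification the article gives for the size of the trial, and it concerns the primary outcome. The Abstract says the aim is to find which of the two approaches is more effective, and the Discussion expects the results to inform how rehabilitation resources are allocated. If the power is really about 44%, a non-significant result says little. A reader who trusts the stated 80% could still take it as evidence that NVT is no better than individualized therapy.

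**Working it through.** **Inputs, all from the Sample size section:** n = 10 per group, 1:1; difference 0.63; SD 0.74; alpha 0.05. Sidedness is not stated, so both are shown, with two-sided as the usual default.

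**1. Power of a two-sample t-test with 10 per group.**
- Standardized difference: d = 0.63/0.74 = 0.8514.
- Noncentrality: d × √(n/2) = 0.8514 × √5 = 1.904, with 18 degrees of freedom.
- Two-sided power: 43.7% (normal approximation 47.8%).
- One-sided power: 57.4% (normal approximation 60.2%).

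None of these is near 80%, so the plan's figure is not reproduced.

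**2. Sample size for 80% power.**
- Normal formula, two-sided: 2 × (1.960 + 0.842)²/0.8514² = 21.7, so 22 per group.
- Exact t-test, two-sided: 22 per group gives 78.8% and 23 gives 80.6%, so 23 per group (46 in total).
- Exact t-test, one-sided: 17 per group gives 78.4% and 18 gives 80.5%, so 18 per group.

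**3. What 10 per group can detect (two-sided).**
- 80% power requires d = 1.325, a difference of 1.325 × 0.74 = 0.98. Relative to plan this is 0.98/0.63 = 1.56.
- Suppose the trial observed exactly 0.63 with SD 0.74. The standard error is 0.74 × √(2/10) = 0.331, so t = 0.63/0.331 = 1.90 and p = 0.073. The 95% confidence interval has half-width 2.101 × 0.331 = 0.70. The planned effect, observed exactly, would not reach two-sided significance.

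**4. The planned ANCOVA.** Take 0.74 as the unadjusted SD and let r be the correlation between baseline and three-month scores. The residual SD is 0.74 × √(1 − r²), the noncentrality is 1.904/√(1 − r²), and there are 17 degrees of freedom. Power with 10 per group:

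| r | two-sided | one-sided |
|---|---|---|
| 0.3 | 46.9% | 60.7% |
| 0.5 | 54.5% | 67.9% |
| 0.6 | 61.2% | 73.8% |
| 0.7 | 71.0% | 81.9% |
| 0.75 | 77.4% | 86.8% |

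Power of 80% is reached at r = 0.768 two-sided and r = 0.679 one-sided. If 0.74 is already a residual SD, ANCOVA brings no gain and two-sided power stays at about 44%.

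**5. Where 10 might come from (conjecture).** A one-sample or paired t-test with n = 10 at one-sided 0.05 has noncentrality 0.8514 × √10 = 2.692 on 9 degrees of freedom, and power 79.9%. Of the variants tried, this is the only one that gives 80% from the stated inputs alone, but it does not apply to two independent groups. Leaving the factor 2 out of the normal formula gives 21.7/2 = 10.8, which is close but would round up to 11. The documents confirm neither route, and the conclusion does not depend on them.

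**The case against.** The strongest objection is that the 44% belongs to a test the trial will not use. The planned analysis is ANCOVA on the baseline score, and at any appreciable positive correlation it has more power if 0.74 is the unadjusted SD: 54.5% at r = 0.5 and 71.0% at r = 0.7, two-sided. With a one-sided test, r of about 0.68 would be enough for 80%. The article does not say which kind of SD 0.74 is, and a condensed article may leave the formula, the sidedness and an assumed correlation to the full protocol.

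Part of this stands. The 44% must be labelled as the unadjusted two-sided figure. It is also too strong to say without condition that the trial will more likely than not miss the planned effect: that holds on the stated inputs with a two-sided test, but not at r = 0.5 or above, nor for a one-sided test.

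The objection does not rescue the statement. The Sample size section ties 80% power to the difference, the SD and alpha alone, and those inputs do not give 80% with either sidedness. Reaching it takes a correlation of about 0.77 (0.68 one-sided) that the article does not mention. Leaving out a correlation is not the defect; the defect is a stated power that the stated inputs contradict. Calling 20 a minimum does not help either, because the sentence attaches the 80% to exactly 10 per group.

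**Conclusion.** The concern holds. On the plan's own inputs, 10 per group gives 43.7% power two-sided (57.4% one-sided) for an unadjusted comparison, against the 80% stated. Reaching 80% takes 23 per group two-sided, which is 2.3 times the planned number.

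This rests on reading 0.74 as the between-patient SD that applies to the comparison, and on equal groups with no losses. Any dropout from the 20 would lower the power further. ANCOVA could narrow or close the gap, but only with a strong baseline correlation that would have to be stated and supported.

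**What to change.** Correct the power statement in the Sample size section in one of three ways.

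1. **Keep 20 patients and restate the power.** For example: 'With 10 per group, an unadjusted two-sided t-test at 0.05 has about 44% power for a difference of 0.63 with SD 0.74; the difference detectable with 80% power is 0.98. On these inputs 80% power needs 23 per group.' Add that the estimate will be reported with its 95% confidence interval and that non-significance will not be read as equal effectiveness. Describing the trial as preliminary would fit this size.
2. **Base the calculation on ANCOVA.** State the sidedness, whether 0.74 is the unadjusted SD, and the assumed baseline to three-month correlation with its source. Give the power over a range of correlations, as in the table above.
3. **Enlarge the trial** to 46 evaluable patients on the stated inputs, plus an allowance for dropout.

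The first option costs one corrected paragraph and a less favourable stated power, with no extra patients. The second also needs a defensible correlation. The third needs 26 more evaluable patients (46 − 20).

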#### Statistical analysis

Data will be entered into an SPSS database with all identifying details removed. An ANCOVA will be performed to compare outcomes between the intervention groups, controlling for initial scores as covariates in the analyses.

Statistical analyses will be undertaken using SPSS version 17.0 Statistical software. All analyses will on an intention to treat basis and will be blinded (i.e. groups identified by number only) and results published according to the Consort Statement formal.

## Discussion

Visual rehabilitation training is routinely provided for people with hemianopia following stroke however the benefits of visual rehabilitation training on functional outcomes have not been well evaluated. Despite us knowing it is important to rehabilitation as it impacts negatively on independence following stroke [4].

The goal of visual rehabilitation involves making the most of a person's residual vision, specifically to try to overcome the visual disabilities that are most troublesome to them. Part of the difficulty in evaluating the effectiveness of vision rehabilitation in homonymous hemianopia is the varied type of strategies used by therapists. At the moment the details of the rehabilitation program are negotiated between each patient and their rehabilitation therapist. No robust evidence currently exists to identify the most effective way to deliver vision rehabilitation in people with homonymous hemianopia after a stroke or the optimum time required [13].

There is evidence that providing more exercise therapy early after stroke improves peoples' ability to recover [29] but the effects of additional therapy in vision rehabilitation are unclear. No large scale randomized controlled trials have been performed to establish the effectiveness of visual rehabilitation following brain damage [13].

This project will compare the effectiveness of current visual rehabilitation protocols which vary in type and dosage according to individual clinicians' recommendations, to a new standardized technology (NVT). Functional outcome measures, such as performance on a mobility assessment course and scanning ability will be employed as well as patient reported outcomes such as, vision specific health related quality of life to allow a meaningful assessment of this rehabilitation intervention.

A debate exists around the mechanisms which underlie the remedial approach in visual rehabilitation following stroke, that is compensatory or neuroplasticity [7]. The outcome of our proposed study will contribute to the knowledge of the mechanisms behind the compensatory approaches, currently used in clinical practice. Furthermore, the results of the trial will provide information that will inform the allocation of resources in visual rehabilitation post stroke. This is in terms of dosage and type of therapy provided.

As in many areas of rehabilitation more rigorous research is needed to identify which remedial approaches should be included in clinical practice for visual loss following stroke.
